### Secondary aims

Examine the effects of the therapy on participants’ health and well-being, and its safety profile (see table 2).

**Table 2 T2:** Clinical, safety and exploratory outcomes

Area	Measure	Timepoint
Clinical		
Quality of life	Assessment of Quality of Life 8-dimension scale (AQoL-8D)^42 43^	Baseline, Week 10, 20 and 32
Functioning	Work and Social Adjustment Scale (WSAS)^44^	Baseline, Week 10, 20 and 32
Depression, anxiety and stress symptoms	Depression, Anxiety and Stress Scale 21 (DASS-21)^45^	Baseline, Week 10, 20 and 32
Severity of illness and perceived improvement	Patient Global Impression scale (PGI)—severity and improvement^46 47^	Baseline (severity subscale only), Week 10, 20 and 32
Physical symptoms	30-item participant self-report Debilitating Symptom Complexes Attributed to Ticks (DSCATT) symptom scale developed by our research group	Baseline, Week 10, 20 and 32
Psychological flexibility	Comprehensive assessment of Acceptance and Commitment Therapy processes (CompACT)^48^	Baseline, Week 20 and 32
Clinician* rated severity of illness and perceived improvement	Transdiagnostic Clinical Global Impression (T-CGI) scale^49^	Baseline (severity subscale only), and treatment endpoint, that is, after completion of the participants 16th treatment session
Safety		
Safety of the intervention	Adverse events, as reported by the participant, and/or as observed by study staff	Assessed at each session by trial therapists; assessed at Week 10 and Week 20 by project coordinator (waitlist controls)
	Negative Effects Questionnaire (NEQ)—20 item^28^	Postintervention (Week 20) for therapy randomised, and treated waitlist controls
Exploratory		
Preliminary cost-effectiveness of the intervention	Healthcare resource use and cost, and lost productivity (absenteeism and presenteeism). Obtained via participant self-report on a tailored resource use questionnaire (RUQ) and supplemented by Medicare Benefits Scheme/Pharmaceutical Benefits Scheme (MBS/PBS) data from Services Australia (where specific consent is provided to access this data).	Baseline, Week 20 and Week 32 (RUQ); MBS/PBS data obtained for 3 months prior to randomisation (to reflect the same reporting time frame as RUQ) up until 8 months post randomisation
Brain activity	Task-based (emotional Stroop) and resting-state fMRI Blood Oxygen Level Dependent (BOLD) signal	Baseline and post-treatment (20 weeks after completion of the intervention)

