### Intervention

#### Therapy arm

Therapy will consist of 16 sessions delivered by a psychologist via Telehealth or face-to-face at the Austin Hospital. The first session will be 90 min, whereas follow-up sessions will be 60 min. Sessions will be delivered weekly as much as possible; however, participants will have 20 weeks to complete all 16 sessions to accommodate for cancellations.

The therapy is a hybrid, based on principles of ACT, but including several elements from Cognitive Behavioural Therapy. Delivery is guided by a purpose-written therapist manual and corresponding participant workbook. Development of the therapy, including patient involvement and integration of their feedback can be read in detail here ([name] *et al*, in submission). Manualised modules include (1) education on concepts of health and illness and the neurobiology of symptom experience in DSCATT, (2) core principles of ACT, (3) evaluating the daily routines, (4) increasing levels of activity, (5) identifying and connecting with values, (6) setting goals, (7) strategies for managing uncertainty of illness. Additional modules on self-compassion, improving sleep, addressing difficulties with thinking and memory, and navigating social relationships will be administered according to participant need. See online supplemental table S1 for an outline of content covered in each session.

Trial clinicians will have the capacity to flexibly adapt individual sessions to suit the presenting needs of participants. The participant will decide which is the most pressing issue/problem for them. This will guide the order of delivery of modules between session 6 and 10, contingent on where the participant is currently at in their therapy trajectory.

Participants will be provided with homework tasks each week via email, to be completed between sessions to practise introduced skills and concepts. They will be encouraged to set aside up to 1 hour per week to complete these tasks. Homework worksheets provided to the participants are included in the participant workbook. A reminder email or SMS, based on the participants’ communication preferences, will be delivered during the week to follow-up on homework tasks. A review of homework tasks will be performed each session, including whether the participant completed the set homework and discussion of progress and any challenges experienced.

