### Waitlist control arm

Individuals who are assigned to the waitlist control group will be encouraged to continue their treatments as usual. They will be sent study questionnaires at Baseline, and 10, 20 and 32 weeks postrandomisation. In addition, the project coordinator will telephone participants at Week 10 and Week 20 to review the occurrence of adverse events (AEs) (to serve as a comparator to the therapy arm). After completion of the Week 32 questionnaires, participants will be offered access to the 16-session therapy, if desired. If they choose to proceed, they will be sent additional study questionnaires to complete 10 weeks and 20 weeks after commencing their first therapy session.

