#### Safety monitoring

Our definition, assessment and recording of AEs and harms of treatment will be informed by Klatte *et al*^29 30^ and the National Health and Medical Research Council (NHMRC) safety monitoring and reporting guidelines.^31^ AEs may include worsening of pre-existing symptoms, recurrence of previous symptoms not present/disclosed at randomisation, diagnosis of a new medical condition and/or emergence of new symptoms or injuries.

The occurrence of AEs in participants randomised to receive the therapy will be reviewed by the trial therapists during each treatment session and documented in REDCap as necessary. AEs will include those reported by the participant and those observed by the trial therapist. The severity and causality of events to the therapy, and other study procedures, will be rated by both the participant and the medical monitors. The medical monitors will be unblinded to group allocation so details of the participants progress in therapy can be discussed (as relayed by the participant’s trial therapist) and ascertained if related to the AE. Waitlist control participants will be telephoned at Week 10 and Week 20 by the project coordinator to determine the occurrence of AEs. All AEs will be followed up until stable/resolved. Verbal consent will be required from the participant to be followed up if AEs persist at Week 32.

All safety reporting in the study will follow the Sponsor’s (Austin Health) current safety reporting guidelines.

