#### Safety outcomes

AEs will be summarised descriptively by treatment group, including the number of AEs and the number of participants with at least one AE. Summary statistics will be presented for the full measure and for each of the factors of the NEQ.

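### Adverse events are collected by different means in the two arms, so the descriptive between-arm safety summary is confounded by ascertainment

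*Protocol article*

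**What the plan says.** **Therapy arm.** Under Safety monitoring: "The occurrence of AEs in participants randomised to receive the therapy will be reviewed by the trial therapists during each treatment session". The same section adds: "AEs will include those reported by the participant and those observed by the trial therapist". Under Therapy arm, "participants will have 20 weeks to complete all 16 sessions to accommodate for cancellations".

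**Waitlist arm.** Under Safety monitoring: "Waitlist control participants will be telephoned at Week 10 and Week 20 by the project coordinator to determine the occurrence of AEs". Under Waitlist control arm, the stated purpose of these calls is "to serve as a comparator to the therapy arm". Table 2 repeats the split: "Assessed at each session by trial therapists; assessed at Week 10 and Week 20 by project coordinator (waitlist controls".

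**Analysis.** Under Safety outcomes: "AEs will be summarised descriptively by treatment group, including the number of AEs and the number of participants with at least one AE". No test is planned.

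**Definition.** Under Safety monitoring, an AE may be a worsening of symptoms already present or a return of earlier ones, as well as a new diagnosis, symptom or injury. The case definition in Table 3 describes an illness that relapses, remits and varies over time.

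**Contacts common to both arms.** Under Study questionnaires, both arms are sent questionnaires at Weeks 10, 20 and 32 after randomisation, whatever session has been reached. The article does not place AE questions in them. The Negative Effects Questionnaire (NEQ) goes only to people who have had the therapy.

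**The concern.** The arms differ in how often AEs are sought, who asks, whether the contact is a therapy session or a telephone call, how far back the person must remember, and whether a clinician's observation counts. Symptoms that come and go are the events most sensitive to these differences: a bad week mentioned at the next session may be forgotten by a call up to ten weeks later.

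The article says the waitlist calls exist to provide a comparison, but the method does not give a like-for-like one. An analysis plan cannot repair this later, because events that nobody asked about cannot be recovered. An excess of AEs on therapy could be an artefact of asking, and a genuine excess could be dismissed as that artefact. The introduction notes that psychological treatment of unexplained syndromes can attract controversy, so the by-arm AE table is likely to be read closely.

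A second gap concerns therapy participants who stop attending. Their only scheduled AE review is the session, so after stopping they have none, while waitlist participants still receive their calls.

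**Working it through.** The article gives no AE rate, AE precision or AE sample size, so there is no planned figure to reproduce. The check has two parts.

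**1. Contacts, from the document.** Therapy arm: up to 16. Waitlist: 2. At full attendance the ratio is 16/2 = 8 to 1. At an assumed 10 attended sessions it is 10/2 = 5 to 1.

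**2. Illustration of size when the arms truly do not differ.**

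Inputs from the document: 120 randomised 1:1, so 60 per arm; 20 weeks; 16 sessions; calls at Weeks 10 and 20.

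Assumptions, not in the document: a true rate of λ = 1 AE per person per 20 weeks in both arms, and a chance of reporting an event at the next contact that halves every H weeks. H is varied from 2 weeks to perfect recall.

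Formulas, with k = ln 2 / H:
- fraction captured over a gap of g weeks = (1 − e^(−kg)) / (kg)
- arm capture c = the sum over gaps of g × that fraction, divided by 20
- recorded AEs = 60 × λ × c
- participants with any AE = 60 × (1 − e^(−λc))

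Worked case, H = 4 weeks, sessions evenly spread (g = 20/16 = 1.25), k = 0.1733:
- therapy: kg = 0.2166, c = (1 − 0.8052)/0.2166 = 0.899
- waitlist: g = 10, kg = 1.733, c = (1 − 0.1768)/1.733 = 0.475
- ratio = 0.899/0.475 = 1.89
- recorded AEs: 54 vs 29; participants with any AE: 36 vs 23

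All values, 16 sessions spread over 20 weeks:

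| H (weeks) | Capture, therapy vs waitlist | Recorded AEs | Ratio | Participants with any AE |
|---|---|---|---|---|
| 2 | 0.812 vs 0.280 | 49 vs 17 | 2.90 | 33 vs 15 |
| 4 | 0.899 vs 0.475 | 54 vs 29 | 1.89 | 36 vs 23 |
| 8 | 0.948 vs 0.669 | 57 vs 40 | 1.42 | 37 vs 29 |
| 16 | 0.973 vs 0.812 | 58 vs 49 | 1.20 | 37 vs 33 |
| perfect recall | 1.000 vs 1.000 | 60 vs 60 | 1.00 | 38 vs 38 |

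The AE ratio does not depend on λ, which cancels.

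Two other attendance patterns, AE ratio at H = 2, 4, 8, 16 and perfect recall:
- 10 sessions spread over 20 weeks: 2.58, 1.78, 1.37, 1.18, 1.00.
- 16 weekly sessions ending at Week 16, with no AE review from then to Week 20: 2.42, 1.55, 1.15, 0.96, 0.80. With perfect recall the therapy arm captures 16/20 = 0.80 of events and the waitlist all of them.

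**With common ascertainment.** If both arms are asked at the same times, with the same questions and the same look-back, c is the same in both arms and the ratio is 1.00 at every H.

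The model covers only timing and recall. It leaves out the change of asker and mode, the therapist's own observations, and early stopping.

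**The case against.** The strongest reply is that little hangs on this table. The primary aim is feasibility, safety is a secondary aim, the trial is not designed to detect a treatment effect, and the AE summary has no test, rate ratio or decision rule. That stands, and it lowers the priority.

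The defence also limits several stronger readings that a reader might infer:

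- *The by-arm table shows only how often people were asked and cannot be interpreted.* This goes too far. The two calls can cover the same 20 weeks as the sessions, and with evenly spread sessions and perfect recall the frequency effect vanishes. The count of people with any AE is also planned, and in the table above it is distorted less than the event count.
- *The therapy is bound to look more harmful.* The direction rests on assumed recall and attendance. Events after the last session can go unasked in the therapy arm, and the ratio can then fall below 1.
- *Harms in people who stop therapy go unrecorded.* Table 2 allows any participant report or staff observation. The NEQ goes to everyone who takes part in the therapy, withdrawn participants may attend the feedback interview, reasons for withdrawal are noted, and known AEs are followed until stable or resolved. What is missing is a scheduled AE check.
- *The 60% retention figure implies that 24 of 60 therapy participants would be without a check.* That figure is a hypothetical completion rate for all 120 participants, not a stopping rate in one arm.
- *The lack of a scheduled AE check between Weeks 20 and 32 biases the comparison.* It applies to both arms alike, so it is a question of completeness.

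None of this supplies a common AE source for the two arms. The NEQ cannot serve, because untreated waitlist participants do not receive it.

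**Conclusion.** The point holds as a moderate one. The unequal ascertainment is plain in the text, and it conflicts with the stated purpose of the waitlist calls. The descriptive between-arm AE summary is confounded by frequency, asker, mode and look-back, and it should not be read as a like-for-like comparison.

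The size is not known from the document. With no true difference, the scenarios examined give recorded-AE ratios from about 0.8 to 2.9. They assume recall half-lives from 2 weeks to perfect recall and either 10 or 16 sessions attended. These are illustrations, not bounds. More recorded AEs on therapy is the likelier direction, because frequent asking and therapist observation both add events, but a reversal is possible.

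**What to change.** 1. **Common source.** Add identical AE questions, with the same look-back, to the Week 10, 20 and 32 questionnaires already sent to both arms. Alternatively, extend the coordinator's Week 10 and Week 20 calls, with one script, to every therapy-arm participant, including those who have stopped sessions.
2. **Analysis.** Base the between-arm AE summary on that common source only. Report session-found AEs separately, as safety monitoring of the therapy arm.
3. **Participants already past those timepoints.** Recruitment was expected to run from June 2023 to October 2025, so there may be many. For them, drop or qualify the description of the waitlist as a comparator, report AEs by source, and state the unequal ascertainment as a limitation. Keep their data apart from those collected under the common schedule.

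**Cost.** Either a few extra questionnaire items, or about 60 × 2 = 120 short calls. Calls at Week 32 in both arms would add up to 120 more. Both options need an amendment, and a change made part-way leaves earlier and later participants with different AE collection. If the trial is too far advanced, step 3 alone costs only wording and table layout.

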### Exploratory aims

Explore potential mediators of treatment response (treatment expectancy, and cognitions and behaviours), cost-effectiveness of the intervention and functional neuroimaging correlates of DSCATT and response to therapy (see table 2). In addition, we will explore changes in clinical outcomes over time in treated waitlist control participants.

### Hypotheses

We hypothesise that the therapy will be practical, acceptable and in-demand for people with DSCATT. Given this is a feasibility trial, any hypothesis testing between the treatment groups will be limited and will therefore be interpreted alongside the magnitude and direction of the treatment effect estimate and two-sided 95% CI (where applicable).

## Methods and analysis

### Trial design

A 32-week, individually randomised, waitlist-controlled, parallel convergent mixed-methods feasibility and pilot trial involving adults (≥18 years) located in Australia with DSCATT. This study will collect quantitative and qualitative data to address its study aims.

Participants will be randomly assigned in a 1:1 ratio to receive 16 sessions of ACT-informed therapy, delivered one-to-one by a trial therapist within a 20-week period and adjunctive to their pre-existing healthcare with follow-up at 32 weeks OR participants will be assigned to the waitlist control group where they will continue their treatment as usual for 32 weeks. After control participants complete the 32-week waitlist, they will be offered access to the 16-session therapy with a trial clinician.

### Participants

#### Eligibility criteria

The trial will recruit adults 18 years of age and older who have access to Telehealth facilities or are able to attend on site at the Austin Hospital (Heidelberg, VIC, Australia). Participants will be assessed by a trial physician to determine if they meet the research case definition for DSCATT. The case definition was developed by our research group via a modified Delphi process involving clinicians, researchers and patient representatives, in combination with analysis of a DSCATT patient and healthy control self-report symptom dataset. Additional eligibility criteria are outlined in table 3.

**Table 3 T3:** Eligibility criteria

Inclusion criteria	Exclusion criteria
Able to consent to the study Adults ≥18 years of age Meet the trial’s case definition for Debilitating Symptom Complexes Attributed to Ticks (DSCATT): *DSCATT requires evidence of a tick bite* which must be: Subject report of an observed tick bite (though symptoms may not develop for several months afterwards) OR serological results from a NATA-accredited laboratory consistent with previous infection (ie, detection of pathogen-specific IgG) with a tick-transmitted pathogen, for example, *Rickettsia*, Q-fever, *Babesia*, *Anaplasma*, *Borrelia* or tick-borne encephalitis virus DSCATT can be acquired in *Australia or overseas* DSCATT *must involve symptoms in three or more systems* (cardiovascular, musculoskeletal, neurological, etc) which *must include fatigue and a cognitive* *symptom* DSCATT symptoms can be mild, but *must be present for at least 6* months, including relapse and remission and *must impact everyday* *activities* DSCATT can develop following one or more diagnosed infections, or without diagnosed infection DSCATT is excluded by other medical conditions which better explain the symptoms, but not by abnormal tests in isolation, nor by other medically unexplained syndromes Other supporting (although not mandatory) criteria: DSCATT can involve pain DSCATT can involve neuropathy (weakness, nerve pain, numbness or tingling) A person with DSCATT may have had a rash (including but not limited to, erythema migrans) as part of their illness Symptoms of DSCATT can vary in type and intensity, within the same person over time. Access to Telehealth facilities/able to attend on site. Possess English sufficient to engage in the treatment programme and answer self-report questionnaires. Able to pause any existing psychological therapies during the treatment intervention.	Current psychotic disorder as per Mini International Neuropsychiatric Interview (MINI) assessment. Diagnosis of a medical condition which better explains the participant’s symptoms (excluding medically unexplained syndromes/functional disorders).

* This case definition was developed in 2022 and updated in 2024 following a modified Delphi process facilitated by our research group involving patient representatives, clinicians and scientists familiar with DSCATT.

NATA, National Association of Testing Authorities (Australia).

#### Study setting

The trial will be conducted remotely via telehealth, or in-person at the Austin Hospital for those who prefer to attend on site. An optional pre–post-treatment neuroimaging component will be conducted at the Melbourne Brain Centre Imaging Unit (MBCIU; University of Melbourne, Parkville, VIC, Australia).

#### Recruitment

Recruitment is anticipated to occur from June 2023 until October 2025. The trial will be advertised via a patient advocacy and tick-borne illness education organisation, the Karl McManus Foundation, who will circulate Human Research Ethics Committee (HREC)-approved recruitment flyers to their members. Clinicians and researchers known to work with DSCATT patients may also distribute these flyers to suitable candidates with a study invitation letter, if desired. In addition, the trial website will be listed on the Australian Government Department of Health’s tick bite associated illness in Australia website. If required, we will engage a clinical trial recruitment agency to obtain suitable candidates.

Study staff will respond to inquiries and address queries where applicable (via telephone/email, as preferred by the person inquiring). Candidates interested in participating in the study will be briefly telephone screened by the project coordinator to ascertain their age, diagnosed medical conditions, current symptoms and treatments. They will be sent the participant information and consent form (PICF) via email/post (as they prefer) and be asked to review in their own time. A suitable time to follow-up with the candidate will be arranged to address any further queries, and to book in their medical screening appointment if they wish to proceed with the trial.

#### Consent

Written, informed consent will be required for study participation, and prior to completing the medical screening appointment to assess eligibility. PICFs will be issued to study candidates by the project coordinator via email/post, as preferred (see online supplemental material ‘PICF Master FIND trial V.3.3’). After reviewing the PICF, candidates may have as much time as desired while recruitment for the trial is open to consider participating. Informed consent procedures may be completed by the project coordinator or the trial physician. Participants will have the option to consent via one of three ways: (1) Face-to-face with study staff, (2) E-consent via Research Electronic Data Capture (REDCap),^24 25^ (3) Informed consent completed via telehealth/telephone, and a signed hard copy of the consent form returned via post or scanned and emailed to study staff. All consent forms will be co-signed by study staff who completed informed consent with the participant, and a copy of the dually signed consent form will be sent to the participant.

Participants may be asked to re-consent to the study if terms of consent change. For example, if study procedures are amended during the trial which affects how participant data is used, participants will be contacted to discuss this change and be asked to sign an updated PICF, if willing.

